# ABSTRACT

Male circumcision (MC) reduces, by more than half, the risk of HIV-1 acquisition. WHO and UNAIDS recommend that “*male circumcision should be recognized as an efficacious intervention for HIV prevention especially in countries and regions with heterosexual HIV epidemics and low male circumcision prevalence.*[1]” As a result, programs have been introduced and scaled up for voluntary medical male circumcision. Kenya leads with the largest expansion of services. Early resumption of sexual intercourse after MC may have deleterious effects, including higher rates of post-operative surgical complications, and higher HIV acquisition among females in couples that resume sexual activity before certified wound healing. In the context of rapid scale-up of MC, adherence to post-operative clinic appointments allows clinicians to assess wound healing and to deliver risk reduction counseling. Abstinence from sexual intercourse before complete wound healing would reduce the rate of post-operative adverse events and minimize the risk of HIV transmission from HIV-infected men to their uninfected female partners. To our knowledge, the effect of reminders delivered via text messaging to promote adherence to clinic visits and abstinence after MC has not been investigated. We propose a randomized controlled trial in which men who will have undergone voluntary medical male circumcision at selected sites in Kisumu will be randomized to receive either the intervention (context-sensitive text messages after circumcision) or the control condition (usual care). This study seeks to determine (a) the effect of regular text messages sent to men after circumcision on attendance of the scheduled 7-day post-operative clinic visit versus usual care; (b) the proportion of men who resume sexual activity before 42 days post-procedure after receiving regular text messages versus usual care within the 42 days post-circumcision; and (c) to identify potential predictors of failure to attend the scheduled 7-day post-operative visit and early resumption of sexual intercourse.

# LIST OF ACRONYMS

| AE | Adverse Experience |
| --- | --- |
| AIDS | Acquired Immunodeficiency Syndrome |
| CI | Confidence Interval |
| CMR | Center for Microbiology Research |
| CONSORT | Consolidated Standards of Reporting Trials |
| ERC | Ethical Review Committee |
| FWA | Federalwide Assurance |
| HIV | Human Immunodeficiency Virus |
| ID | Identification number |
| IRB | Institutional Review Board |
| KEMRI | Kenya Medical Research Institute |
| MC | Male Circumcision |
| MOH | Ministry of Health |
| NRHS | Nyanza Reproductive Health Society |
| NIH | National Institutes of Health |
| OPRR | Office of Protection from Research Risks |
| PI | Principal Investigator |
| SAE | Serious Adverse Experience |
| SMS | Short Messaging Service |
| STD | Sexually Transmitted Disease |
| UNAIDS | Joint United Nations Program on AIDS |
| UNIM | A partnership between the Universities of Nairobi, Illinois, and Manitoba (PI [name]) |
| WHO | World Health Organization |

# INTRODUCTION

## Background

The epicenter of the HIV epidemic remains in sub-Saharan Africa, with 1.9 million new infections in 2008 [2]. Male circumcision (MC) reduces, by more than half, the risk of HIV-1 acquisition [3-5]. WHO and UNAIDS recommend that “*male circumcision should be recognized as an efficacious intervention for HIV prevention especially in countries and regions with heterosexual HIV epidemics and low male circumcision prevalence.* [1]” As a result, programs have been introduced and scaled for voluntary medical male circumcision in several sub-Saharan countries, with Kenya leading with the largest expansion of services (approximately 40,000 MCs done by October, 2009) [6].

Early resumption of sexual intercourse after the MC may have deleterious effects. A study of adverse events related to MC found that post-operative surgical complications occur at higher rates among men who resume sexual intercourse before wound healing is complete than among those who delay resumption of intercourse [7]. In a study assessing the effect of MC on male to female transmission of HIV, higher HIV acquisition occurred among females in couples who resumed sexual activity early (before certified wound healing) compared to those who did not resume sex early [8].

In the context of rapid scale-up of MC, adherence to post-operative clinic appointments is important. It gives clinicians an opportunity to assess wound healing, and provides additional opportunities to deliver risk reduction counseling. Abstinence from sexual intercourse before complete wound healing is vital in order to reduce the rate of post-operative adverse events in both HIV infected and uninfected men, as well as to minimize the risk of HIV transmission from HIV-infected men to their uninfected female partners. To our knowledge, the effect of reminders delivered via SMS to promote adherence to clinic visits and abstinence after MC has not been investigated.

## Benefits of delayed resumption of sex after MC

Delayed resumption of sex after MC potentially reduces the risk of HIV acquisition during the wound healing period. During the healing period, men who engage in sexual activity may be at an increased risk of acquiring HIV infection, though studies on this question remain inconclusive. One study found that sex early after circumcision (less than 42 days after the procedure) was not associated with increased risk of HIV seroconversion, but concluded that the study was underpowered [9]. The authors also concluded that the possibility of increased risk of HIV acquisition still remains. Further, these results were obtained under circumstances that included intensive counseling for trial participants to delay sexual activity until wound healing. Certainly, there is biological plausibility for an increased risk of acquiring infections, including HIV, from sex occurring before wound healing.

For HIV-positive men in discordant relationships, there is the added advantage of reduced risk of transmission to their female partners [8]. A significant reduction in the rates of post-operative surgical complications has also been documented for both HIV-infected and uninfected men who delay resumption of sex [7].

## Counseling for MC

During the conduct of the randomized trials of MC for HIV prevention, participants received intensive counseling on HIV/STI prevention at each trial visit. In the Kisumu trial, for example, risk-reduction counseling was individually-tailored for each participant at every visit [4]. In the setting of programmatic MC in Kenya, counseling is less intensive than was the case in the trials. There is a need to find ways of reinforcing HIV prevention counseling among men who have undergone circumcision. To our knowledge, no interventions to address this gap have been investigated. We therefore propose to compare the current standard of care to text messaging as a simple, affordable and appropriate intervention.

The overall aim of this intervention is to ensure that circumcised men have additional opportunities to receive HIV prevention messages most pertinent to their circumcision status. Ensuring that circumcised men return for the scheduled 7-day follow-up visit should provide additional opportunity for counseling, as well as ensure that clinicians assess wounds for healing. Regular text messages sent after circumcision should also fortify HIV prevention messages already received at the clinic. We hypothesize that this intervention will lead to an increased rate of return for the scheduled 7-day post-operative visit, and a reduced rate of early resumption of sexual intercourse before wound healing.

# RATIONALE

## Studies of medical and behavioral interventions delivered via phone

The use of reminders delivered via communications technology enhances the effectiveness of medical interventions. A randomized controlled trial comparing diabetes control among patients who transmitted their blood glucose levels to a clinic via phone (treatment group) to those who physically went to the clinic with results (control) found better blood glycemic control in the treatment group (lower HbA1c) [10]. In the United States, an RCT compared follow-up phone call by a pharmacist 2 days after discharge from hospital to no phone call and found the phone call group more satisfied with discharge instructions (86% vs. 61%, *P* = 0.007) [11]. Another RCT found a significant improvement in adherence to antihypertensive medication among patients who used a telephone reminder system in addition to usual medical care (P = .03), with a significantly lower mean diastolic blood pressure (P = .02) [12].

## Telephone reminders and adherence to clinic appointments

With regard to improving adherence to scheduled clinic appointments, telephone reminders lead to higher attendance rates. A study among attendants at an adolescent clinic found that the attendance rate was significantly increased when a telephone reminder was given one day before a clinic appointment, compared to no reminder [13]. SMS text reminders have also been shown to significantly improve clinic attendance. A cohort study in Australia found the rate of failure to attend clinics much lower among patients who received an SMS reminder (14.2% v 23.4%; *P* < 0.001) [14].

## Mobile telephone technology in developing countries

Most studies on the topic of delivery of medical and behavioral interventions using telephone systems have been conducted in developed countries that have a high coverage of telephones with robust communication networks. However, the recent rapid increase in mobile telephony in developing countries presents a new avenue for similar interventions. In Kenya, mobile cellular subscription has grown from 0.4 per 100 people in 2000 to 30.2 per 100 people in 2007, with 77% of the population covered by a mobile cellular network [15]. A 2006 survey in an economically-disadvantaged part of Nairobi found that 89% of respondents had access to a mobile phone [16]. Respondents in that survey also found mobile phones acceptable for receiving HIV-related information. In South Africa, mobile telephone technology used to monitor adherence to highly active antiretroviral therapy was found to be acceptable to both patients and providers [17].

The feasibility of using mobile phones in public health interventions in developing countries has been demonstrated. A study in Peru demonstrated the feasibility of using mobile telephony to collect data on adverse effects caused by metronidazole therapy for treatment of sexually transmitted infections in remote communities [18]. SMS text messaging has also been employed with much success in improving adherence to treatment in a South African tuberculosis program [19].

The Nyanza province of Kenya has a high HIV prevalence (14.9%) and low prevalence of male circumcision (48.2%) [20]. In Kisumu, the largest town in Nyanza, only about 10% of adult Luo males are circumcised [4]. This has made it the province of priority in terms of implementing voluntary medical male circumcision programs. Since the launch of the Kenya Ministry of Health’s Voluntary Medical Male Circumcision program, there has been a high uptake of MC services in this region. This rapid growth in the MC program is likely, in the long term, to result in a significant reduction in HIV incidence and prevalence with a public health impact. In order to insure these gains, it would be important to investigate strategies to mitigate any potential hindrance.

## Study Generalizability

This study will help to evaluate a strategy to improve adherence to post-operative clinic visits and reduce early resumption of sex after MC. If proven superior to usual care, the proposed intervention (regular, context-based text-messaging) can be easily integrated into existing healthcare systems in resource-limited settings. Findings from this study will provide randomized trial evidence that will inform HIV prevention program planners and implementers in Kenya and beyond.

# STUDY OBJECTIVES AND HYPOTHESES

The general objective of this study is to evaluate an intervention that will promote adherence to post-operative clinic visits, and open up additional opportunities for circumcised men to receive HIV prevention messages (at the clinic and on their mobile phones), such as the benefits of abstinence until wound healing, and the harmful effects of early resumption of sexual intercourse.

## Specific Objectives

**Objective 1:** To determine the effect of regular, context-sensitive text messages sent to men after undergoing circumcision versus usual care on attendance of the scheduled 7-day post-operative clinic visit, in a randomized controlled trial.

**Hypothesis 1:** We hypothesize that men who receive the SMS intervention will have higher rates of attendance at the 7-day post-operative visit, compared to those receiving usual care.

**Objective 2:** To determine the proportion of men who resume sexual activity before 42 days post-procedure (wound healing is expected to be complete in the majority of circumcised men within 42 days [7]) after receiving regular, context-sensitive text messages versus usual care within the 42 days post-circumcision.

**Hypothesis 2a:** We hypothesize that men who receive the SMS intervention will report higher rates of abstinence from sex during the 42 days post-circumcision, compared to those receiving usual care.

**Hypothesis 2b:** We also hypothesize that, among those who resume sex before 42 days post-procedure, those who receive the messages resume sex later than those who do not.

## Secondary Objective

To identify potential predictors of failure to attend the scheduled 7-day post-operative visit, and also to identify potential predictors of early resumption of sex after MC.

## Study Outcome Measures

### Primary Outcome Measures

The primary outcome measure for objective 1 is the proportion of men failing to return for a post-operative clinic visit at 7 days. This proportion will be determined by examining each participant’s clinic records after their 7th post-operative day. Adherence to this clinic visit will be analyzed as a dichotomous variable. Participants will be considered to have ‘attended’ or ‘not attended’ the clinic visit after the elapse of 3 days after the scheduled 7-day visit.

The primary outcome measure for objective 2 is the proportion of men who report resumption of sexual activity before 42 days post-circumcision. This proportion will be determined by self-report using a brief questionnaire delivered via SMS. The analysis will be as a dichotomous variable, with participants considered as having either ‘resumed’ or ‘not resumed.’ Among men who resume sex before 42 days post-circumcision, we will also compare the time to resumption by study arm.

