## Inclusion Criteria

Participants who meet the following criteria will be eligible for enrollment:

1. Male
2. 18 years or older
3. Have undergone circumcision on the day they are screened for the study
4. Currently own a mobile phone with text-messaging capability, and
5. Have the mobile phone in their possession at the time of enrollment
6. Able and willing to respond to a questionnaire administered via a phone call

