## Enrollment Visit

Enrollment into the study will occur on the same day as screening. While still in the private counseling room, participants who are found to be eligible will be offered enrollment into the study. Study procedures will then be described in detail and participants asked to provide written informed consent prior to enrollment. The informed consent form will also request participants’ permission to access their MC clinic records. The informed consent process is described in section 10.1 below.

After the informed consent process, study staff will abstract demographic information from a participant’s clinic file. Data collected will include *client number, mobile phone number, date of MC, date of birth, ethnic origin, district of residence, sub-location/estate of residence, education level, employment status, marital status, religion, age at first sex, number of sex partners in last month, whether subject has ever been tested for HIV, whether client was given condoms, how client learnt about MC services, referral source, and cadre of person who performed procedure.* HIV status and/or test results will NOT be collected as part of this study. Study staff will also administer a brief questionnaire to all participants (appendix III)*.*

Following enrollment, participants will be randomized to either of the study arms. Randomization procedures are described in detail in section 3.5 above. Participants’ mobile phone numbers will be confirmed using an SMS-based registration system. This will involve sending a text message from a participant’s phone to a phone number controlled by our robotic software. The text message will contain the time of day that they find most suitable for messages to be sent to them as well as the language in which they prefer to receive text messages (from a choice of English, Swahili, or Dholuo). Upon receiving this initial text message, the software will decipher the contents and also store the subject’s phone number. The software will have been pre-programmed to send specific text messages to those in the intervention arm, one on each day at the time and in the language specified by the subject for the first 7 days post-procedure. Details are provided in section 5 below. Participants will be reminded of all study procedures again before leaving the clinic.

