The proportion of circumcised men who reported early resumption of sexual activity in the South African MC trial was **0.225** [9]. This trial was selected because the counseling regimen used was designed to approximate programmatic implementation of MC. Assuming that the proportion of men resuming early sexual intercourse is 0.225 among the control group, a 2-sided test with a significance level of 0.05, beginning with 600 men in each arm and about 11% loss to follow-up at 42 days, with **532 men** remaining in each arm we will have at least **80% power** to detect a relative risk between the two arms of **0.70** or larger.

The following table summarizes the range of sample sizes required with different assumptions of the true relative risk of failure to return for subjects in the intervention arm relative to controls:

|  | RR = 0.50 | RR = 0.60 | RR = 0.65 | **RR = 0.70** | RR = 0.75 | RR = 0.80 |
| --- | --- | --- | --- | --- | --- | --- |
| Sample Size (per arm) **90% power** | 231 | 381 | 510 | 712 | 1048 | 1674 |
| Sample Size (per arm) **80% power** | 173 | 285 | 382 | **532** | 783 | 1251 |

[figure not shown]

Our enrollment target will therefore be1,200 participants (600 per arm).

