**Testable Hypothesis 2:**

A chi-square test will be used to compare the proportions of men resuming early sexual intercourse (defined as resuming sex before 42 days post-procedure) by study arm. A follow-up analysis comparing the proportions resuming early sexual intercourse will also be done that further adjusts for variables that were imbalanced between arms at baseline.

Among men who report early resumption of sexual intercourse, the time to resumption (in weeks from MC procedure to resumption) of sexual intercourse will be compared by study arm using Kaplan-Meier plots, log-rank tests, and Cox regression. A follow-up analysis comparing the time to resumption will also be done that further adjusts for variables that were imbalanced between arms at baseline.

We will also conduct a multivariable analysis to estimate the effect of resumption of sex as a function of several factors.

Among men who report early resumption of sexual intercourse, the number of sex partners (binary; 1 versus 2 or more) will be compared by study arm using a Chi-Square test. A relative risk and 95% confidence interval will be calculated.

Among men who report early resumption of sexual intercourse, the proportion of men reporting unprotected sexual intercourse will be compared by study arm using a Chi-Square test. A relative risk and 95% confidence interval will be calculated.

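### The Objective 2 comparison leaves unused a likely strong predictor recorded before randomisation; stratifying it by baseline sexual activity would gain precision at almost no cost

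*Protocol*

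**What the plan says.** **Outcome.** Protocol, Primary Outcome Measures: "The primary outcome measure for objective 2 is the proportion of men who report resumption of sexual activity before 42 days post-circumcision". The coding has two categories: "The analysis will be as a dichotomous variable, with participants considered as having either" resumed or not resumed. Hypothesis 2a (Specific Objectives) is framed as abstinence: "men who receive the SMS intervention will report higher rates of abstinence from sex during the 42 days post-circumcision".

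**Who is included.** The six inclusion and three exclusion criteria do not mention sexual history. The criterion tied to surgery is only "Have undergone circumcision on the day they are screened for the study".

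**Baseline data.** The Enrollment Visit section lists "age at first sex, number of sex partners in last month" among the items taken from the clinic file. The Allocation concealment section places this abstraction before the envelope is issued.

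**Test.** Under Testable Hypothesis 2: "A chi-square test will be used to compare the proportions of men resuming early sexual intercourse" by arm. A follow-up analysis adjusts for variables found imbalanced at baseline. A separate multivariable analysis of resumption is mentioned without naming its factors.

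**Planning rate.** Sample Size Justification: "The proportion of circumcised men who reported early resumption of sexual activity in the South African MC trial was" 0.225, and then "Assuming that the proportion of men resuming early sexual intercourse is 0.225 among the control group".

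**The concern.** Men with no partner or no sexual experience before surgery can enter the trial. Those who stay abstinent are scored as not having resumed, alongside men who abstained because of the messages. Prior sexual activity is therefore likely to predict the outcome strongly. The trial holds that information before allocation, but its primary test ignores it. The adjustment rule selects covariates by chance imbalance rather than by how well they predict the outcome, so a strong but balanced predictor would never be used.

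There is also a gap in the definition. With only two categories, the protocol does not say whether a man who first has sex within 42 days has resumed.

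At stake are some precision in a primary comparison sized with almost no reserve, and the effect among men who were active before surgery, which no planned analysis reports.

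**Working it through.** **Inputs from the protocol.** Control rate 0.225; RR 0.70, so the intervention rate is 0.225 × 0.70 = 0.1575 and the difference is 6.75 points; two-sided 5% level; 532 men per arm after about 11% loss from 600.

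**Inputs assumed.** The documents do not give the share of men inactive before surgery, f; take 20% to 50%. They do not give the control event rate q among those men; take 5% or 10%. RR is 0.70 in both strata.

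**1. Reproduce the plan.** The pooled-variance formula without continuity correction gives 532 per arm for 80% power, as stated. As a power calculation:
- Expected score: d = n(p0 − p1)/2 = 532 × 0.0675/2 = 17.955.
- Null variance, with mean rate 0.19125: V0 = (532/2) × 0.19125 × 0.80875 = 41.14.
- Alternative variance: V1 = (532/4) × (0.225 × 0.775 + 0.1575 × 0.8425) = 40.84.
- Power = Φ[(d − 1.96√V0)/√V1] = Φ[(17.955 − 12.572)/6.391] = Φ(0.842) = 80.0%.

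**2. Stratify, keeping every man.** Hold the overall control rate at 0.225, so the rate a in active men is (0.225 − f·q)/(1 − f). The score d is unchanged. V0 and V1 become sums over the two strata, weighted by (1 − f) and f.

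Example, f = 50%, q = 5%: a = (0.225 − 0.025)/0.5 = 0.40.
- V0 = 266 × [0.5 × 0.34 × 0.66 + 0.5 × 0.0425 × 0.9575] = 35.26.
- V1 = 133 × [0.5 × (0.40 × 0.60 + 0.28 × 0.72) + 0.5 × (0.05 × 0.95 + 0.035 × 0.965)] = 34.77.
- Power = Φ[(17.955 − 11.638)/5.897] = Φ(1.071) = 85.8%.

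| f | Crude | Stratified, q = 5% | Stratified, q = 10% |
|---|---|---|---|
| 20% | 80.0% | 81.5% | 80.8% |
| 30% | 80.0% | 82.5% | 81.3% |
| 40% | 80.0% | 83.9% | 82.0% |
| 50% | 80.0% | 85.8% | 83.0% |

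Simulation of the Mantel-Haenszel test agrees to within about half a percentage point.

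**3. Effect in active men.** With q = 5% the control rate in active men is 0.269, 0.300, 0.342 and 0.400 for f = 20%, 30%, 40% and 50%. Multiplying by 0.30 gives risk differences of 8.1, 9.0, 10.3 and 12.0 points, against 6.75 points over all men. The RR is 0.70 throughout.

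**The case against.** **No power is lost against the plan.** This stands. The protocol words 0.225 as a rate in circumcised men generally, so an all-men rate is matched to an all-men test and 80% is correct. A reader might infer that men with nothing to resume leave the trial underpowered. That requires 0.225 to be a rate among active men only: crude power would then be 74.8% at f = 10% and 61.9% at f = 30%, with no events in inactive men. It could also arise if inactive men are commoner here than in the source trial. Nothing in the document supports either.

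**The absolute effect is readable.** This stands too. A reader might infer that the overall risk difference means little. But every man in the intervention arm is texted and Hypothesis 2a is not limited to active men. The all-men difference is a legitimate quantity for a programme that would text all circumcised phone owners. It is simply not the effect among previously active men.

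**Inactive men can still have sex before healing.** True, and this is why q is not set to zero. It also argues against reserving the event for previously active men, which would discard the behaviour the trial wants to prevent.

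**The coding is inferred, and details may sit in the SAP.** The day-42 questionnaire was not available, and supportive tables often belong in an SAP. But the protocol itself fixes the primary test, the two outcome categories and the adjustment rule. The secondary objective on predictors, and the unspecified multivariable analysis, do not bring baseline activity into the primary comparison.

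**Conclusion.** The point holds as one of efficiency and definition. Randomisation protects the comparison between arms, the RR is not distorted, and the stated 80% power stands if 0.225 is an all-men rate. What the plan gives up is precision from data it already collects: roughly 1 to 6 percentage points of power for f of 20% to 50% with q of 5% or 10%. The gain is near the lower end if few men are inactive or if their event rate is not much lower than that of active men. These figures rest on assumed f and q, a common RR of 0.70 and complete recording of the baseline items. The definition of the event for men with no prior activity needs settling whatever the size of the gain.

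**What to change.** 1. **Primary Outcome Measures:** state that any sexual intercourse before day 42 is the event for every man, including men with no earlier sexual activity.
2. **Testable Hypothesis 2:** keep all randomised men with day-42 data, analysed as assigned. Replace the crude chi-square as the primary Objective 2 comparison with a Mantel-Haenszel test and RR stratified by baseline sexual activity. Define that as having ever had sex and having at least one partner in the last month, with levels yes, no and not recorded. The crude comparison can be reported alongside.
3. **Same section:** pre-specify a supportive table of proportions, RR and risk difference in men active before surgery. It should be fixed before outcomes are seen, because an at-risk group chosen afterwards would not be credible.

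The cost is wording in two sections and one table, with no new data or participants. The stratifier is self-reported and imperfect. Because it is recorded before allocation, misclassification reduces the gain in efficiency but does not affect the validity of the stratified comparison.
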